## 7.2.2 Analysis of the Primary Outcome Measure

The primary outcome will be analyzed for the ITT population. Based on our primary aim and primary outcome, we hypothesize that the probability of treatment engagement at 7 days is greater among participants with OUD in the XR-BUP arm versus those in the SL-BUP arm, i.e., XR treatment is superior to SL.

The probability  $p_{XR}$  represents the probability of treatment engagement for a subject in the XR arm at Day 7, and the probability  $p_{SL}$  represents the probability of treatment engagement for a subject in the SL arm. Treatment superiority is operationally defined in terms of the odds ratio,

$$OR = [p_{XR} * (1 - p_{SL})] / [p_{SL} * (1 - p_{XR})]$$

Thus, the primary statistical hypotheses are:

$$H_0: OR = 1, \text{ i.e., XR is not superior to SL}$$

$$H_A: OR \neq 1, \text{ i.e., XR is different than SL}$$

An  $OR > 1$  and  $p\text{-value} < 0.05$  will indicate superiority of XR over SL with regard to the treatment engagement outcome.

The primary outcome, treatment engagement at 7 days (Y/N), will be assessed for the ITT population. Treatment engagement will also be assessed at 30 days. Treatment differences (XR vs. SL) for this dichotomous outcome will be examined using weighted GEE. The traditional GEE approach is valid under the strong assumption that missing data is missing completely at random

(MCAR). Robins, Rotnitzky and Zhao proposed an extension of GEE called the weighted GEE to alleviate this restrictive assumption. The weighted GEE provides consistent parameter estimates when the dropout mechanism is correctly classified by implementing the inverse-probability weighted method to account for dropouts under the missing at random (MAR) assumption. Inverse probability weights are estimated by a logistic regression of dropout at a particular measurement occasion. The dropout model will include baseline demographic and clinical characteristics including treatment engagement prior to enrollment, site, treatment group, insurance status and time as well as outcomes at previous timepoints. From the dropout model, predicted probabilities of dropout will be estimated for each subject at each post-randomization timepoint. The predicted probabilities will then be translated into weights where the weight is the inverse of the cumulative probability of dropping out at a particular assessment. Prior to final analysis, weights will be evaluated for outliers ( $>3$ ). If identified, additional covariates in the logistic model and/or trimming of weights will be considered to correct for this. The weighted GEE model will contain an effect for intervention (XR vs. SL). An exchangeable working correlation will be used to account for clustering responses from the same participants (i.e., 7 and 30 days). The model will also include treatment engagement in prior 12 months from baseline, age, sex, ethnicity/race, insurance status and site (see **Exhibit 2** below). Linear contrasts will be used to estimate odds ratios, treatment differences and 95% confidence intervals for the proportions of participants that engage in treatment in XR vs. SL at both 7- and 30-days follow-up.

The following SAS System code will be used for the GEE analyses. The variables in the models are as follows:

- *primdat*: primary outcome analysis file,
- *patid*: patient ID,
- *site*: site ID,
- *site2*: site ID with small sites ( $\leq 20$  randomized) pooled into one site,
- *treat*: treatment arm - XR-BUP or SL-BUP,
- *engage*: engagement variable where 1 = engaged and 0 = not engaged,
- *exist*: 1 if *engage* is not missing and 0 if *engage* is missing,
- *visit*: study visit (Day 7 or Day 30),
- *gender*: categorical variable for gender,
- *race\_cat*: categorical variable for White, Black, Other race, unknown or not reported,
- *ethnic\_cat*: ethnicity category for Hispanic, not Hispanic, unknown or not reported,
- *insurance\_rand*: categorical variable for insurance status used for randomization - private, public, or no insurance,
- *prior\_engagement*: ?

1. Compute the weights for Day 7. The weights will be  $1/\text{pred07}$  where *pred07* is the probability that the outcome variable is not missing.

```
proc logistic data = primdat;
  class exist site site2 (ref = '02156') patid trt (ref = 'SL-BUP')
    gender (ref = '1') race_cat (ref = '1') ethnic_cat (ref = '0')
    insurance_rand (ref = '1') / param = ref;
  model exist (desc) = trt site2 age gender race_cat ethnic_cat
    insurance_rand /*prior_engagement*/;
  output out = denom07 predicted = pred07;
  where visno = 'C07';
run;
```

2. Compute the weights for Day 30. The weights at Day 30 are cumulative and will be computed as  $(1/\text{pred07}) * (1/\text{pred30})$ .

```
proc logistic data = primdat;
  class exist site site2 (ref = '02156') patid trt (ref = 'SL-BUP')
    gender (ref = '1') race_cat (ref = '1') ethnic_cat (ref = '0')
    insurance_rand (ref = '1') engage07 / param = ref;
  model exist (desc) = trt site2 age gender race_cat ethnic_cat
    insurance_rand /*prior_engagement*/ engage07;
  output out = denom30 predicted = pred30;
  where visno = 'C30';
run;
```

3. Run the final model with the computed weights. Treatment effects will be assessed at each visit using the *diffs* output from the *lsmeans* statement.

```
proc genmod data = final;
  class engage site site2 (ref = '02156') patid trt (ref = 'SL-BUP')
    visno (ref = 'C07') gender (ref = '1') race_cat (ref = '1')
    ethnic_cat (ref = '0') insurance_rand (ref = '1');
  model engage (desc) = trt visno trt * visno site2 age gender race_cat
    ethnic_cat insurance_rand /*prior_engagement*/ /
    dist = bin link = logit;
  weight wgt;
  repeated subject = patid / corr = cs;
  lsmeans trt * visno / pdiff oddsratio cl;
  output lsmeans = lsmeans diffs = diffs;
run;
```

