### 8.3.2 Exclusion Criteria

All patients enrolled into the study must not:

1. Have urine toxicology test that is positive for methadone
2. Be pregnant as determined by human chorionic gonadotropin (hCG) testing at the index ED visit
3. Have a medical or psychiatric condition that requires hospitalization.
4. Opioid administration (excluding BUP) at the index ED visit, prior to enrollment, and COWS remains  $< 4$  during ED stay
5. Be actively suicidal or severely cognitively impaired precluding informed consent
6. Present from an extended care facility (e.g., skilled nursing facility)
7. Require continued prescription opioids for a pain condition
8. Be a prisoner or in police custody at the time of index ED visit
9. Be currently (anytime within the past 14 days) enrolled in formal addiction treatment, including by court order. Patients enrolled in formal addiction treatment who are not receiving MOUD are eligible
10. Be unable to provide reliable locator information including 2 contact numbers in addition to their own
11. Be unwilling to follow study procedures (e.g., unwilling to provide permission to contact referral provider/program or unavailable for the follow-up assessments)
12. Have prior enrollment in the current study component

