### 7.2.3 Supportive Analyses of the Primary Outcome Measure

The primary outcome will be analyzed as above for the PP population.

Given the relative advantages of Generalized Estimating Equations and generalized linear mixed models (GLMM), sensitivity analyses will compare treatments using a logistic regression with SAS PROC GLMMIX, with a random effect for subject.

```
proc glimmix data = primdat;
  class engage site site2 (ref = '02156') patid trt (ref = 'SL-BUP')
    visno (ref = 'C07') gender (ref = '1') race_cat (ref = '1')
    ethnic_cat (ref = '0') insurance_rand (ref = '1');
  model engage (event = '1') = trt visno trt * visno site2 age gender
    race_cat ethnic_cat insurance_rand /*prior_engagement*/ /
    dist = bin link = logit;
  random _residual_ / subject = patid type = cs;
  weight wgt;
  lsmeans trt * visno / pdiff oddsratio cl;
run;
```

Additional sensitivity analyses may be conducted to evaluate the effect of changes in eligibility criteria.

The supportive analyses of the primary outcome will be analyzed for the ITT and PP populations.

Subgroup analyses for sex, race, ethnicity, and age will be performed as required by the NIH (NIH, 2016). The proportions and confidence intervals for each of the primary outcome measures will be estimated in the following subgroups for the ITT population:

- 1) Males and females

- 2) Black, White, and all other races
- 3) Hispanic and non-Hispanic participants
- 4) Participants older than the median age and those equal to or younger than the median age.

The primary analysis will be re-run with a covariate for the subgroup and the interaction between the subgroup and treatment. Estimate statements will be used to determine the treatment effects and associated confidence intervals for each group.

Additional subgroups of interest include the following:

- 1) Housing status at baseline (unstable housing in last 12 months (DM1.DMNIGHT = yes versus no); currently in unstable housing (DM1.DMLIVING = yes versus no))
- 2) Fentanyl positive (UDS.UDFEN1 = positive) and fentanyl negative (UDS.UDFEN1 = negative) from baseline UDS
- 3) Stimulant positive (UDS.UDAMP1 = positive or UDS.UDMET1 = positive) and stimulant negative (UDS.UDAMP1 = positive and UDS.UDMET1 = positive) from baseline UDS
- 4) Treatment seeking at the index ED visit (EDR.ERPRBTYP = 'Seeking referral for OUD treatment' versus other reasons)
- 5) Overdose at the index ED visit (EDR.ERPRBTYP = 'Overdose' versus other reasons)

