#### **7.2.7 Missing Data**

Several strategies were imposed to accommodate the likelihood that missing data will occur during this study including prevention, strict data collection procedures, careful selection of variables without large proportions of missing values, and regular monitoring of the trial. Despite these prevention efforts it is reasonable to assume missing data will occur. Our proposed primary and secondary analyses make use of all available data and are valid under the assumption that missing data will be missing at random (MAR) (Diggle, et al., Molenberghs, et al.). We may evaluate the plausibility of this assumption by determining the extent of missing data and use logistic regression to identify factors associated with missing data. We may conduct sensitivity analysis using a pattern-mixture approach implemented using multiple imputation under missing not at random (MNAR) assumptions to examine the robustness of conclusions of the primary analysis to missing data (Little, et al., Molenberghs, et al.).

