## 10.2 RCT Component

A sample size of 850 per group/treatment arm was required to ensure 90% power at the two-sided 0.05 significance level to detect a difference in the proportion engaged in formal addiction treatment at Day 7 of 8 percentage points between SL-BUP and XR-BUP, assuming 45% engaged for SL-BUP and 53% engaged for XR-BUP. This is calculated based on a simple two-sample proportion test. This sample size also provides greater than 80% power to detect improvements of 7% (as opposed to 8%). Given the conservative nature of a 45% estimate in the control group (SL-BUP) used, any actual rate in the control group would allow at least 80% power to detect a treatment effect of 7% and at least 90% power to detect a treatment effect of 8%. A sample size of approximately 2,000 was then chosen to accommodate a roughly 15% dropout rate. Power estimates for differing rates in the SL-BUP group and treatment effects are provided in Figure 1.

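### Protocol and SAP prose define the primary-analysis weight the wrong way round; the SAP code has it right, but the Day-30 weight step and the GLMM check do not do what the text says

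*Combined protocol and SAP*

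**What the plan says.** **Weight, in prose.** Protocol 12.6.3.2 and SAP 7.2.2 describe a logistic model for dropout and then say that "the weight is the inverse of the cumulative probability of dropping out at a particular assessment". SAP 7.2.2 adds a check for outlying weights, set at above 3.

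**Weight, in code.** The SAS steps in SAP 7.2.2 model the indicator that the outcome is present. The Day-7 weight is 1/`pred07`, where `pred07` "is the probability that the outcome variable is not missing". The Day-30 weight is (1/`pred07`) × (1/`pred30`). The protocol contains no code.

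**Day-30 weight model.** Its predictor list ends "insurance_rand /*prior_engagement*/ engage07". `engage07` is a CLASS variable. No level for a missing value is shown, and the variable is absent from the SAP's variable list. SAP 7.2.7 states: "Our proposed primary and secondary analyses make use of all available data".

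**GLMM sensitivity analysis.** SAP 7.2.3 describes a logistic mixed model with a random subject effect. The code has "random _residual_ / subject = patid type = cs" and carries the weight variable of the primary analysis.

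**Prior engagement.** The text requires it in both the dropout model and the outcome model. In SAP 7.2.2 its definition is a question mark, in Exhibit 2 its variable name is blank, and it is commented out of all four models in 7.2.2 and 7.2.3.

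**The concern.** Inverse-probability weighting corrects for missing outcomes by letting each observed person stand in for similar people who were lost, so those most at risk of loss get the largest weights. Dividing by the probability of dropping out does the reverse: it gives the largest weights to the people least like those lost. The two documents therefore state a rule for the primary endpoint that the SAP's own code contradicts, and a reader of the protocol alone has only the wrong rule.

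The other two items are also gaps between text and code. Missingness here need not be monotone. Day 7 and Day 30 are separate telephone contacts, and under SAP 7.2.1 an outcome is also missing when a named facility does not verify. Someone can be missing at Day 7 and observed at Day 30, and the code has no place for that person. The GLMM is the only alternative model to which the plan commits itself: the per-protocol analysis repeats the primary model, and the missing-not-at-random analysis in SAP 7.2.7 is optional. If that check is nearly the primary model again, it adds little.

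**Working it through.** **1. The plan's own figures.** SAP 10.2 states: "A sample size of 850 per group/treatment arm was required to ensure 90% power at the two-sided 0.05 significance level", "assuming 45% engaged for SL-BUP and 53% engaged for XR-BUP". The usual two-proportion formula gives 819 per arm, or 844 with continuity correction. At 850 per arm, power is 91.0% for 8 points and 82.4% for 7 points, so the stated 90% and 80% are met. 1,700 / 0.85 = 2,000, and 15% of 2,000 is 300 expected missing.

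**2. Size of the weights.** Let d be the probability of dropout. The code weight is 1/(1 − d) and the prose weight is 1/d.

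| d | code 1/(1 − d) | prose 1/d |
|---|---|---|
| 0.05 | 1.053 | 20.0 |
| 0.15 | 1.176 | 6.67 |
| 0.30 | 1.429 | 3.33 |

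The prose weight exceeds 3 whenever d is below 1/3; the code weight does so only when d is above 2/3. A screen at 3 therefore makes sense only for the code.

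**3. Effective sample size.** This uses the Kish formula, (Σw)²/Σw². Assume two equal halves with dropout 5% and 25% (mean 15%). The observed shares of those randomised are 0.475 and 0.375, together 0.85.
- Code: Σw = 0.475/0.95 + 0.375/0.75 = 1.000; Σw² = 0.475/0.95² + 0.375/0.75² = 1.193; effective size 1/1.193 = 0.838 N.
- Prose: Σw = 0.475 × 20 + 0.375 × 4 = 11.0; Σw² = 0.475 × 400 + 0.375 × 16 = 196; effective size 121/196 = 0.617 N.

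**4. Effect on the treatment odds ratio.** I simulated 2,000,000 participants with one binary baseline stratum, logistic outcomes and an independence working correlation. About 14% were missing at Day 7 and 26.5% at Day 30. All parameters are assumptions.

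| Odds ratio | full data | code | prose |
|---|---|---|---|
| Day 7, same effect in both strata | 1.373 | 1.373 | 1.375 |
| Day 7, effect differs by stratum | 1.373 | 1.374 | 1.189 |
| Day 30, same effect in both strata at Day 7 | 1.482 | 1.484 | 1.530 to 1.547 |
| Day 30, Day-7 effect differs by stratum | 1.483 | 1.485 | 1.486 to 1.491 |

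The Day-30 prose range covers two readings of a cumulative dropout probability. At Day 7 the variance inflation from the weights was 1.01 (code) and 1.24 (prose). No code weight and every prose weight exceeded 3.

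**5. Day-30 outcomes lost.** By default, a record with a missing CLASS predictor gets no predicted value. With `engage07` missing there is no `pred30`, hence no weight, and PROC GENMOD omits the Day-30 record. Of about 300 participants missing at Day 7, suppose 10%, 25% or 50% are reached at Day 30. Then 30, 75 or 150 observed outcomes are lost. The reach rates are assumed. The Day-30 code column in step 4 already excludes these records: 1.484 against 1.482 with full data.

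**6. The GLMM.** A `_residual_` random statement models the residual covariance (R-side). With compound symmetry and the same weights, it is a marginal model close to the GEE. A model with a true subject effect estimates a different quantity. For 45% against 53%, the marginal odds ratio is (0.53 × 0.55)/(0.45 × 0.47) = 1.378. The subject-specific odds ratio is 1.47, 1.70 or 2.01 if the random-intercept SD is 1, 2 or 3.

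**The case against.** The strongest reply is that SAP 7.2.2 names its code as what will be run, and that code weights Day 7, the primary endpoint, correctly. The faulty sentence sits in a paragraph that otherwise describes the standard method, and the screen at 3 shows which rule was intended. This stands. A reader might infer that the primary GEE itself is mis-specified; the coded Day-7 step does not support that. What remains is a wrong sentence in both documents, in a protocol with no code to set against it.

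A second reply is that every covariate in the coded Day-7 weight model is also in the outcome model, so even the wrong weights need not bias the adjusted odds ratio. This also stands where the effect is the same across strata (1.375 against 1.373). A reader might instead build a one-group example. With halves at 5% and 35% dropout and 60% and 30% engagement, the prose weights turn a true 45.0% into 57.3%. That is an unadjusted mean at 20% average dropout, not the planned treatment contrast, so it is not evidence of bias in the treatment effect.

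Third, the Day-30 loss leaves the Day-7 weights untouched, concerns a secondary outcome and, under missing at random, mainly costs precision. It also presumes that `engage07` is left blank for non-responders. All of this is fair, but the plan still claims to use all available data, and as shown the code would not.

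Fourth, the RCT sections are a declared first draft, with v4.0 to finalise them before database lock (SAP 14.3 and Exhibit 5). That explains the placeholders and makes correction cheap. It is no reason to leave opposite rules standing in an open-label trial.

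**Conclusion.** The point holds as a contradiction between text and code, not as a fault in the coded primary analysis. The weight sentence is wrong in both documents and must be corrected. If followed, it would raise the weight at 15% dropout from about 1.18 to about 6.7. In the two-stratum example it would cut the effective sample from 0.838 N to 0.617 N. It could shift the Day-7 odds ratio (1.37 to 1.19 in one assumed scenario), but only where the treatment effect varies with predictors of dropout. The simulations do not cover borrowing between visits through the exchangeable correlation.

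The Day-30 code loses an assumed 30 to 150 observed outcomes, mainly a loss of precision on a key secondary outcome. The GLMM check is mislabelled: as coded, it cannot show what a subject-level random effect would change.

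Prior engagement needs a definition and a place in the models, because the text already requires it. Protocol 8.3.2 states: "Patients enrolled in formal addiction treatment who are not receiving MOUD are eligible". A reader might infer from this that omitting the covariate dilutes the treatment difference. The documents do not support that. Any such dilution would come from eligibility, they give no prevalence for these participants, and restoring a covariate for engagement in the prior 12 months would not undo it.

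**What to change.** Before SAP v4.0:

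1. In protocol 12.6.3.2 and SAP 7.2.2, define the weight as the inverse of the cumulative probability of remaining observed.
2. For Day 30, code `engage07` as engaged, not engaged or missing, fit the model to everyone, and weight Day-30 records by 1/P(observed at Day 30). A missing level alone is not enough, because the 1/`pred07` factor would be wrong for people missing at Day 7. Otherwise, withdraw the all-available-data statement in SAP 7.2.7. List `engage07` among the variables.
3. In SAP 7.2.3, use `random intercept / subject=patid` with Laplace or quadrature estimation and report a conditional odds ratio, which should not be expected to equal the GEE estimate. Otherwise, rename the analysis a marginal model. If weights stay in, name the right dataset: the code reads `primdat`, whereas the primary weighted model is run on `final`.
4. Define `prior_engagement`, fill in Exhibit 2, and activate it in the weight and outcome models.

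The cost is one sentence in each document, code edits and one variable definition. Items 1 to 3 need no new data. Item 4 needes a source variable for prior-12-month engagement, which the SAP does not yet name.

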#### 12.6.3.2 Analysis of Primary Effectiveness Outcome

The primary outcome, treatment engagement at 7 days (Y/N), will be assessed for all randomized patients that are enrolled in the study. Treatment engagement will also be assessed at 30 days. Intervention differences (XR vs. SL) for this dichotomous outcome will be examined using weighted GEE. The traditional GEE approach is valid under the strong assumption that missing data is missing completely at random (MCAR). Robins, Rotnitzky and Zhao proposed an extension of GEE called the weighted GEE to alleviate this restrictive assumption. The weighted GEE provides consistent parameter estimates when the dropout mechanism is correctly classified by implementing the inverse-probability weighted method to account for dropouts under the missing at random (MAR) assumption. Inverse probability weights are estimated by a logistic regression of dropout at a particular measurement occasion. Our dropout model will include baseline demographic and clinical characteristics including treatment engagement prior to enrollment, site, intervention group, insurance status and time as well as outcomes at previous timepoints. From the dropout model, predicted probabilities of dropout will be estimated for each subject at each post-randomization timepoint. The predicted probabilities will then be translated into weights where the weight is the inverse of the cumulative probability of dropping out at a particular assessment. The weighted GEE model will contain an effect for intervention (XR vs. SL). An exchangeable working correlation will be used to account for clustering of responses from the same participants (i.e. 7 and 30 days). The model will also include treatment engagement in prior 12 months at baseline, age, sex, ethnicity/race, insurance status and site. Linear contrasts will be used to estimate odds ratios, treatment differences and 95% confidence intervals for the proportions of participants that engage in treatment in XR vs. SL at both 7- and 30-days follow-up. Given the relative advantages of Generalized Estimating Equations and generalized linear mixed models (GLMM) sensitivity analyses will compare treatments using a logistic regression with GLMM, with a random effects for subject. Additional sensitivity analyses may be conducted to evaluate the effect of changes in eligibility criteria.

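### The weighted GEE for engagement pairs visit-specific weights with an exchangeable working correlation, so its Day 30 estimates lack the consistency under missing at random that the SAP claims

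*Combined protocol and SAP*

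**What the plan says.** SAP 7.2.2 builds the weights in two logistic models. The Day 7 weight is 1/pred07, where pred07 "is the probability that the outcome variable is not missing". For Day 30, "The weights at Day 30 are cumulative and will be computed as" (1/pred07)*(1/pred30), and the Day 30 dropout model carries Day 7 engagement as an additive covariate: "insurance_rand /*prior_engagement*/ engage07". It has no treatment-by-engagement term.

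The weights enter PROC GENMOD by a WEIGHT statement, one value per visit row, together with "repeated subject = patid / corr = cs". This is a planned choice, because the SAP text says "An exchangeable working correlation will be used to account for clustering responses from the same participants" and protocol 12.6.3.2 says "An exchangeable working correlation will be used to account for clustering of responses from the same participants".

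The SAP describes the method as the "inverse-probability weighted method to account for dropouts under the missing at random (MAR) assumption", and says it is consistent if the dropout mechanism is correctly classified. One model supplies the Day 7 primary result and the Day 30 formal-treatment result. SAP 7.2.5.1 and 7.2.5.3 send the MOUD engagement outcomes through the same analysis.

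**The concern.** Inverse weighting makes each visit's residual unbiased only when that residual carries its own weight. A non-diagonal working correlation mixes the two visits. The Day 30 equation then contains the Day 7 residual, multiplied by the square root of the product of the two weights and summed over people seen at Day 30. If being seen at Day 30 depends on Day 7 engagement, that sum does not average to zero. Such dependence is the reason for having engage07 in the dropout model. It is also plausible, because under SAP 7.2.1 a participant who is not reached has a missing outcome.

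At stake are the Day 30 engagement proportions and contrasts, which are two of the five key secondary outcomes in SAP 7.2.4. SAP 2.2.5.2 calls the trial open-label, so retention that differs by arm cannot be ruled out.

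**Working it through.** **Inputs.** The plan gives no figure for this bias, so there is none to reproduce.

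- From the documents: Day 7 engagement of 45% (SL-BUP) and 53% (XR-BUP), and 15% dropout (protocol 12.3), read here as 85% observed at Day 7.
- Assumed: Day 30 engagement of 40% and 48%; within-person correlation 0.5 or 0.7; Day 30 retention r0 of 60-80% in XR-BUP participants not engaged at Day 7; a retention odds ratio of 1.5-4.5 for engaged against not engaged.
- Software knowledge, not in the documents: GENMOD's working covariance is V = φ A^½ W^-½ R W^-½ A^½.
- Participants with no Day 7 outcome have no engage07 and so no Day 30 weight. A monotone pattern is therefore used.

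**Step 1: the cross-term.** For someone seen at both visits, with standardised residuals e7 and e30, the Day 30 score is proportional to w30·e30 − α√(w7·w30)·e7. The first part averages to zero at the truth. For the second, w7 = 1/π7, w30 = 1/(π7·r(y7)), and the chance of being seen at both visits is π7·r(y7). The product of that chance and √(w7·w30) is √r(y7), so on the raw scale

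E[√r(y7)·(y7 − μ7)] = μ7(1 − μ7)(√r1 − √r0).

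This is zero only when r1 = r0. Its sign pulls the Day 30 proportion down when engaged people are better retained. With α = 0 (independence) the term disappears.

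**Step 2: numbers, r0 = 60%, odds ratio 4.5.** Odds 1.5 × 4.5 = 6.75, so r1 = 6.75/7.75 = 0.871, and √0.871 − √0.600 = 0.933 − 0.775 = 0.159.

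- XR-BUP: 0.53 × 0.47 × 0.159 = 0.040.
- SL-BUP, same retention: 0.45 × 0.55 × 0.159 = 0.039. The two arms nearly cancel.
- SL-BUP, retention odds 2.7 times those of XR-BUP: r0 = 4.05/5.05 = 0.802, r1 = 18.2/19.2 = 0.948, term = 0.2475 × (0.974 − 0.896) = 0.019. They no longer cancel.
- SL-BUP, retention odds 1/1.65 of those of XR-BUP: r0 = 0.909/1.909 = 0.476, r1 = 4.09/5.09 = 0.804, term = 0.2475 × (0.896 − 0.690) = 0.051. The imbalance is reversed.

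**Step 3: solving the equations in large samples (true weights, arm by visit, correlation 0.5).**

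| Case | Day 30 XR/SL, % (true 48/40) | Day 30 difference (true 8.0) |
|---|---|---|
| Same retention in both arms, r0 60%, OR 4.5 | 45.9/38.0 | 7.9 |
| Same retention in both arms, r0 70%, OR 4.5 | 46.5/38.5 | 8.0 |
| r0 60%, OR 4.5, SL retention odds ×1.65 | | 7.4 |
| r0 60%, OR 4.5, SL retention odds ×2.7 | | 6.9 |
| r0 60%, OR 4.5, SL retention odds ÷1.65 | | 8.6 |
| Working independence, every case | 48/40 | 8.0 |

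With the same mechanism in both arms, over r0 60-80% and odds ratios 1.5-4.5, the arm proportions are 0.4 to 2.1 points low. At correlation 0.7 with r0 60% and odds ratio 4.5 they are about 3 points low. The Day 30 odds ratio stays at 1.385-1.387 against 1.385 at correlation 0.5. If retention does not depend on Day 7 engagement, there is no bias.

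**Step 4: Day 7.** Over SL-BUP retention odds from 1/1.65 to 2.7 times those of XR-BUP, the Day 7 difference moves by at most about 0.2 points at correlation 0.5 and about 0.5 at 0.7.

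**Step 5: the null.** 1,500 simulated trials of 2,000, true 45% in both arms at both visits, weights estimated from the SAP's additive model, retention (not engaged/engaged) 80/97% in XR-BUP and 60/92% in SL-BUP. At correlation 0.5, `corr=cs` gave a Day 30 odds ratio of about 1.05 and type I error of 7.7%. Independence gave 4.9%. The Monte Carlo standard error at 5% is √(0.05 × 0.95/1500) = 0.6 points. At correlation 0.7, `corr=cs` gave 1.085 and 11.7%.

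**Step 6: the software form.** A second placement of the weights, D′V⁻¹W(y − μ) on the observed rows, was also biased. With true Day 30 rates of 45/53% (SL/XR), retention 70/95% and correlation 0.5, it gave 41.8/49.9%.

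**The case against.** The strongest reply is about scope, and much of it stands. Because the same code produces the primary result, a reader might infer that the Day 7 test is compromised. The calculations do not support that: the Day 7 contrast hardly moves. A reader might also infer that the Day 30 treatment effect is biased whenever Day 30 missingness depends on Day 7 engagement. It is not. A material bias in the contrast also needs retention that differs by arm, and the documents give no evidence on either condition.

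The larger figures use strong inputs. With r0 60% and odds ratio 4.5, XR-BUP participants seen at Day 30 are 0.85 × (0.53 × 0.871 + 0.47 × 0.600) = 63%, so 37% are missing, against a planned dropout of 15%. With odds ratio 2, r0 80% and SL-BUP retention odds 1.65 times higher, the difference is 7.8. Converting the 6.9-point case into power at 850 per arm would mislead, since only about 630 XR-BUP and 740 SL-BUP participants per 1,000 would be seen at Day 30.

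Independence is neither sufficient alone nor the only remedy. In a simulated null where retention depended on engagement in XR-BUP (60/95%) but not in SL-BUP (85%), the SAP's additive dropout model was wrong. Independence then gave a Day 30 odds ratio of 1.20, while `corr=cs` gave 1.00 through offsetting errors. Weighting the residuals within the full two-visit covariance also recovered the true values with an exchangeable structure.

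None of this restores the consistency that the SAP claims for the code as written.

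**Conclusion.** The point holds for Day 30. Even with a correctly specified dropout model, the planned combination of weights and working correlation is not consistent under the SAP's own assumption. The consequence is arm-level Day 30 proportions that are modestly too low where engaged participants are better retained. The XR-SL contrast is distorted, in either direction, only where retention also differs by arm. The primary Day 7 comparison is essentially unaffected at correlation 0.5.

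The mechanism follows from the SAP's weights and working correlation, given the assumed form of the WEIGHT statement; the second weight placement shows that it does not hinge on that exact form. The sizes depend on assumed correlation and retention values and should be read as ranges. A larger retention imbalance between arms than those shown would move the contrast further.

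**What to change.** In the weighted GENMOD step of SAP 7.2.2, replace `corr=cs` with `corr=ind` and keep `subject=patid`, so that the robust variance still allows for two outcomes per person. Amend the working-correlation sentence in SAP 7.2.2 and protocol 12.6.3.2 to match. In the same change, add a `trt*engage07` term to the Day 30 dropout model.

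The cost is one keyword, one model term and two sentences, plus a small loss of efficiency. In the simulations at correlation 0.5 with the same retention in both arms, the mean standard error of the Day 30 log odds ratio rose from 0.106 to 0.109 (0.109/0.106 = 1.03), and the Day 7 value stayed at 0.097. SAP 14.3 calls the RCT analyses a first draft, and Exhibit 5 reserves version 4.0 to finalise them before database lock, so the change can be pre-specified there.
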